## STATISTICAL POWER

The sample size has been estimated to provide good statistical power (alpha=0.05, beta=0.90) to detect plausible effects of each intervention. Common assumptions of both sets of power calculations are: 120 clusters, equal randomization between intervention and control and an intra-cluster correlation coefficient of 0.05. These power calculations also assume that there is no interaction between the effects of the package and the effects of salt reduction.

- For the detection of the effects of the package, it is assumed that 8 high risk individuals (20%) will be identified from the 40 survey participants in each cluster, a total of 960 high-risk patients in 120 clusters. Assuming a standard deviation of systolic blood pressure of 15 mmHg, the power to detect a 2.5 mmHg net difference in systolic blood pressure between the intervention and control group pre-post differences will be > 90%. Assuming about half of the high-risk patients will be managed by the village doctors and no difference for those not managed, a 2.5 mmHg difference means a 5 mmHg difference in those actively managed by village doctors. Previous clinical trials demonstrated that even just single drug treatment can lower systolic blood pressure by at least 10 mmHg on average, our targeted blood pressure lowering strategy in package intervention should produce even larger effect. In addition, our CSSS study showed that a low sodium salt substitute could reduce systolic blood pressure by 5.4 mmHg on average. We have reasons to believe that an effect equal or even larger than 5 mmHg systolic blood pressure difference is highly achievable. On the other hand, to achieve a difference smaller than 5 mmHg in systolic blood pressure among those actively managed is not considered meaningful in terms of policy implications. In other words, a smaller effect size is usually not regarded by policy makers as convincing enough for national policies.
- For the detection of the effects of the salt reduction program, assuming a standard deviation of systolic blood pressure of 15 mmHg, the power to detect a 2.5 mmHg net difference in systolic blood pressure between the intervention and control group pre-post differences will be > 90% for a total of 4,800 older adults in the 120 clusters (40 per cluster).

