### The feasibility of implementing a salt reduction program

In 1988, the PI of the present study conducted a small-scale trial to evaluate the feasibility and effect of implementing a salt reduction program in 16 households (38 villagers) in Hanzhong, Shaanxi Province. The results show that, the mean salt intake reduced to 6.1±1.7g/day from 11.1±3.7g/day, after 12-weeks intervention. Average reduction in daily salt intake was 5.0 g, of which 3.9 g/day came from reduced consumption of high-salt food such as preserved vegetables and beans. The urinary sodium and urinary sodium/potassium ratio from 8-hour nightly urinary excretion were all reduced; however, the reductions were not statistically significant. Compared with baseline, the reductions of SBP and DBP were 12.5mmHg and 7.8mmHg (p<0.01 for both). These results demonstrate that simple, clear, and specific dietary instructions on salt reduction can effectively help rural residents reduce their salt intake. Unfortunately, no control group was included in this study.

In 2004-2005 we conducted, in rural China, a randomized trial including 608 high risk individuals recruited from 6 townships (and some 30 villages) in rural and suburban Northern China. Participants were assigned at random to receive either a low-sodium, high potassium salt substitute or continued normal salt. At completion of the 12 months of follow-up systolic blood pressure was 5.4mmHg (95% confidence interval 2.3 to 8.5) lower in the salt substitute group compared to the usual salt group, with evidence that the blood pressure reduction was increasing with time (p=0.001, Figure 1). Adherence to the salt substitute was very high with 98% of participants reporting using the study salt/salt substitute for all or nearly all of their food preparation during the study period.

[figure not shown]

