We conducted another randomized double-blind controlled trial on salt substitute among 220 hypertensive patients and their 348 family members in rural Beijing from 2005-2006. After the one-year intervention, systolic blood pressure reduced by 4.1 (0.8, 7.4) mmHg (measured clinically), 3.1 (0.4, 5.8) mmHg (measured by home monitoring), and 2.4 (-2.4, 5.7) mmHg (ambulatory monitoring) respectively. Among family members, systolic BP by home monitoring reduced by 1.5 (-0.4, 3.4) mmHg, of which family members with hypertension had a reduction of 2.7 (-1.9, 7.2) mmHg and with normal blood pressure, only 0.5 (-1.2, 2.1) mmHg. Reduction in systolic BP was bigger with older age. Further analysis showed that withdrawal from medication was more pronounced in the salt substitute group than control group (normal salt), reaching statistical significance by the 3rd month (p<0.05). During the trial, all (100%) people in the salt substitute group reported consuming the salt provided to them “all” or “most” of the time and 98.2% of the participants in the control group (normal salt) reported so. No between-group difference in compliance was detected (p>0.05).

A similar 3-month randomized single-blind trial conducted in Tibet in 2009 among 284 hypertensive patients showed a bigger reduction [-8.8 mmHg (95% CI: -19.6 to -1.0) systolic and -4.5 mmHg (95% CI: -8.5 to -0.6) diastolic respectively] in this high-altitude area with very high prevalence of hypertension and higher average baseline blood pressure level.

There is currently significant interest in the potential for salt substitutes to decrease vascular disease in China and in Beijing there is a directive requiring greatly increased sales of salt substitute by the Beijing Salt Corporation. Against this background there is a high likelihood that it will be possible to make salt substitute more widely available in rural China and this will be a core component of the salt reduction program.

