### Baseline and follow-up surveys

A baseline and a follow-up random sample survey (2 independent samples) of older adults (50+/60+) will be conducted in all of the 120 villages before and after the interventions. In each village, the survey will collect data from 40 consenting adults, half men and half women. Sampling will be done by the China International Center for Chronic Disease Prevention located in Beijing acoording to village rosters collected before the survey. All age-eligible (50+/60+) villagers will receive a random number. The random numbers will be ranked according to ascending order and informed consents will be sought according to the rank orders until 20 men and 20 women in each village consent to participate in the survey. Efforts to make sure that only one older adult from the same household will be recruited in the survey will be made – through a roster including household information or someone (e.g. village chief) who knows the villagers well enough to identify adults from the same household. Blood pressure, weight, height and heart rate will be measured and recorded according to standardized protocol. A brief questionnaire (see Appendix 2) will be administered by survey staff to collect information on disease history, medication use, care seeking patterns, and lifestyle factors. Survey participants will receive a small gift valued at approximately 5 yuan (RMB) as a token of appreciation for their participation in the survey. Five yuan is approximately half of the minimal wage per hour for hourly workers.

High-risk patients in the evaluation surveys will be defined slightly differently from the high-risk definition in the package. It will be defined as having history of heart disease or stroke; or older age (50+/60+) and having diabetes; or older age (50+/60+) and having a measured systolic blood pressure > 160 mmHg; or older age (50+/60+) and currently on anti-hypertension medication but having ever had a self-reported BP measurement > 160 mmHg. See Appendix 2 for details on identification of high-risk patients from the random sample of older adults.

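### The package's stated power of more than 90% for 2.5 mmHg is about 60% on the protocol's own inputs, and the salt claim holds only for a post-intervention comparison with an SD no higher than about 15.6 mmHg

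*Protocol*

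**What the plan says.** The STATISTICAL POWER section of the protocol aims for "good statistical power (alpha=0.05, beta=0.90) to detect plausible effects of each intervention" (0.90 is evidently the power). The shared inputs are "120 clusters, equal randomization between intervention and control and an intra-cluster correlation coefficient of 0.05". For the package it expects 8 high-risk people among the 40 surveyed per village, "a total of 960 high-risk patients in 120 clusters". For salt the count is "for a total of 4,800 older adults in the 120 clusters (40 per cluster"). Both calculations rest on the same spread: "Assuming a standard deviation of systolic blood pressure of 15 mmHg". No source is given, and no section reports an SD of systolic pressure. Both claims are for a 2.5 mmHg net difference between arms in pre-post change.

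The Baseline and follow-up surveys section specifies "A baseline and a follow-up random sample survey (2 independent samples"), so the same people are not followed. The ANALYSIS PLAN lists a post-intervention comparison first and the net pre-post comparison in addition.

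The section on the feasibility of a salt reduction program reports two sponsor trials from which a spread can be roughly inferred. In 608 high-risk rural people, "systolic blood pressure was 5.4mmHg (95% confidence interval 2.3 to 8.5) lower in the salt substitute group" at 12 months. In 220 rural hypertensive patients, "systolic blood pressure reduced by 4.1 (0.8, 7.4) mmHg (measured clinically").

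**The concern.** The two calculations share every input except cluster size, 8 against 40. The package has one fifth of the participants, yet both claims are more than 90% for the same 2.5 mmHg. The salt claim can be reached from the stated inputs. The package claim cannot.

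The common SD adds a second weakness. It is unsourced, it is applied alike to high-risk patients and to all older adults, and the salt claim has almost no margin above 90%. The contrast matters as well. With independent samples, subtracting a baseline survey adds sampling variance, and it helps only to the extent that village effects persist between surveys.

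What is at stake is how a null result would be read. The protocol treats 2.5 mmHg overall (5 mmHg among managed patients) as the policy-relevant threshold. A non-significant package result could be taken to rule out such an effect, although a true effect of that size would be missed about four times in ten even at SD 15.

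**Working it through.** **Inputs.** From STATISTICAL POWER: difference d = 2.5 mmHg, SD = 15, ICC = 0.05, k = 60 clusters per arm, m = 8 (package) or 40 (salt). Two-sided alpha of 0.05 is my assumption, since sidedness is not stated.

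**Formulas.**
- Post-intervention comparison: SE = SD × √(2 × [1 + (m − 1) × ICC] / (k × m)).
- Net difference, independent samples: SE² = 4 × SD² × [(1 − ICC)/(k × m) + ICC × (1 − r)/k], where r is the correlation of village effects between the two surveys.
- Power = Φ(d/SE − 1.96). Difference detectable with 90% power = 3.24 × SE.

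**1. Package at SD 15.** Design effect = 1 + 7 × 0.05 = 1.35. SE = 15 × √(2 × 1.35/480) = 1.125. Power = Φ(2.222 − 1.96) = 60%. Detectable difference = 3.24 × 1.125 = 3.6 mmHg.
- Net difference: SE = 1.591 at r = 0 (35%) and 1.335 at r = 1 (47%).
- More lenient readings also fall short. One-sided testing gives 72% and ignoring clustering gives 73%. Both together give SE = 15 × √(2/480) = 0.968 and Φ(2.582 − 1.645) = 83%.
- The SD that would give 90% post-intervention is 2.5/(3.24 × 0.075) = 10.3, where 0.075 = 1.125/15.

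**2. Salt at SD 15.** Design effect = 1 + 39 × 0.05 = 2.95. SE = 15 × √(2 × 2.95/2400) = 0.744. Power = Φ(3.362 − 1.96) = 92%, so the stated figure reproduces. The largest SD giving 90% is 2.5/(3.24 × 0.0496) = 15.6, where 0.0496 = 0.744/15.
- Net difference: SE = 1.052 at r = 0 (66%) and 0.597 at r = 1 (99%). For 90%, SE² must be (2.5/3.24)² = 0.595. Since SE² = 0.356 + 0.75 × (1 − r), r must be at least about 0.68.

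**3. What the earlier trials imply.** Assuming equal arms, full follow-up and an unadjusted comparison, SD = (CI width/3.92) × √(N/4).
- 608-person trial: 6.2/3.92 = 1.58; × √152 = 19.5 (18.5 if 10% were lost).
- 220-person trial: 6.6/3.92 = 1.68; × √55 = 12.5.

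**4. Power for 2.5 mmHg by SD.** Net columns run from r = 0 to r = 1.

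| SD | Package, post | Package, net | Salt, post | Salt, net |
|---|---|---|---|---|
| 12.5 | 76% | 47–61% | 98% | 81–99.9% |
| 15 | 60% | 35–47% | 92% | 66–99% |
| 17 | 50% | 28–38% | 84% | 55–96% |
| 18 | 46% | 26–35% | 80% | 51–94% |
| 19.5 | 40% | 23–30% | 73% | 45–90% |
| 20 | 38% | 22–29% | 71% | 43–88% |

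No package cell reaches 90%.

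**The case against.** A reader might infer that the 608-person trial contradicts the SD of 15, and that the SD is why the power claims fail. Neither reading is supported.

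- **Cause.** The package claim already fails at SD 15. Moving to 19.5 explains only the further fall from 60% to 40%.
- **Evidence.** The two trials bracket 15. The 220-person result is worded as a reduction, which may mean changes or adjusted values. But STATISTICAL POWER also describes the 608-person result as a reduction, so wording alone does not justify trusting one and discounting the other. No arm sizes, numbers analysed or models are given. Covariate adjustment would make a back-calculated SD too low; attrition or unequal arms would make it too high.
- **Method.** The same formula applied to the sponsor's 284-patient high-altitude trial (CI −19.6 to −1.0 around −8.8) gives (18.6/3.92) × √71 ≈ 40, and that interval is not symmetric about its estimate. Published intervals are a weak source for a raw SD here.
- **Population.** The salt outcome is in all older adults, of whom the protocol expects 20% to be high-risk. Carrying 19.5 over to them is extrapolation.

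These points stand, and they reduce 19.5 to a sensitivity case. They do not rescue the package figure, which needs no outside SD to refute it.

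In the plan's favour, a 5 mmHg difference across all 8 high-risk people per village would have 99% power at SD 15 (5/1.125 = 4.44). However, the protocol gives 5 mmHg for managed patients only and claims power for 2.5. It is also fair that the ANALYSIS PLAN promises 95% confidence intervals, so the precision achieved will be visible. That limits the harm but does not make the planning statement correct.

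**Conclusion.** The package's claim of more than 90% is wrong as written. On the protocol's own inputs power is about 60% post-intervention and 35% to 47% for the net contrast it names. This rests only on two-sided testing at 0.05 and normal-theory formulas, and relaxing the sidedness or the clustering still leaves it below 90%.

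The salt claim is correct but fragile. It holds for the post-intervention comparison at SD 15 and fails above about 15.6. For the net contrast at SD 15 it holds only if village effects correlate at about 0.68 or more between surveys, and the protocol states no such value.

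The SD of 15 is unsupported, not shown to be too low. If 19.5 applied, post-intervention power would be about 40% (package) and 73% (salt). Both figures depend on unconfirmed assumptions about the 608-person trial, and the salt figure also on extrapolation from high-risk patients.

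**What to change.** In STATISTICAL POWER:

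1. Replace the package's figure of more than 90% with about 60% at SD 15 (post-intervention), and state that the difference detectable with 90% power is about 3.6 mmHg.
2. Say for each figure whether it refers to the post-intervention or the net pre-post contrast. For the net contrast, state the assumed correlation of village effects between surveys.
3. Give a source for the SD, or show power for both interventions over SDs of about 12.5 to 20 as sensitivity, labelling 19.5 as a rough back-calculation.
4. Re-estimate the SD and ICC from the planned baseline survey, separately for high-risk people and all older adults, and update the stated detectable differences.

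Enrolment, visits and data collection do not change. The only cost is a less favourable stated power, above all for the package.

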## ANALYSIS PLAN

The primary analyses will be done by comparing the proportions (F-tests) and means (ANOVA) between the intervention townships and the control townships, separately for each intervention. Not only the point estimates but also estimates of variances will be reported as 95% confidence intervals. We will compare the post-intervention differences in the outcomes between the intervention group and the control group. In addition, we will also evaluate the differences between pre-and-post intervention levels for both the intervention and control group to see if the net differences between the 2 groups are statistically significant.

All analyses will include adjustment for the clustering effect and will be done according to the principle of intention to treat.

In both interventions, the main treatment effect will be assumed to be a fixed effect, while the clusters will be assumed to be random. If there are significant differences in the treatment effect among the clusters, either at a cluster level or an individual level, on any of the baseline characteristics, a multilevel modeling approach will be undertaken.

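### The package comparison has about 60% power for 2.5 mmHg on the protocol's own inputs, not more than 90%

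*Protocol*

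**What the plan says.** The Statistical Power section of the protocol gives inputs common to both interventions: "120 clusters, equal randomization between intervention and control and an intra-cluster correlation coefficient of 0.05", with "good statistical power (alpha=0.05, beta=0.90" as the error rates and no interaction between the two factors. For the package it adds an assumption: "8 high risk individuals (20%) will be identified from the 40 survey participants in each cluster, a total of 960 high-risk patients in 120 clusters". With an SD of 15 mmHg for systolic pressure, it concludes that the "power to detect a 2.5 mmHg net difference in systolic blood pressure between the intervention and control group pre-post differences will be > 90"%.

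The salt bullet repeats that conclusion for the same 2.5 mmHg and the same SD, but with 40 people per village and 4,800 in total.

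The 2.5 mmHg is an average over all high-risk people. The section assumes that about half will be managed and that the rest gain nothing, so it equates to 5 mmHg in those managed. The section calls anything smaller in managed patients too small to matter for policy.

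Two other sections bear on the calculation. Baseline and Follow-up Surveys describes "A baseline and a follow-up random sample survey (2 independent samples") of older adults. The Analysis Plan compares follow-up levels between arms and then, additionally, the net pre-post differences.

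**The concern.** Both bullets give the same effect, SD, ICC, number of villages and power, but the package has one fifth of the people (960 against 4,800). With 8 people per village, sampling error within villages dominates the variance, so the two power figures should differ widely.

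The named comparison makes the package figure harder to reach. Baseline and follow-up are separate samples, so no within-person correlation offsets the baseline sampling error, and a net difference carries the error of both surveys.

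The package effect in high-risk people is the first specific aim, the first null hypothesis and a primary outcome. The hypotheses are framed around an effect large enough for national policy. A reader told that power exceeds 90% at the policy threshold could take a non-significant result as good evidence against a policy-relevant effect. If the figure is wrong, that inference is not available.

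**Working it through.** **Inputs** (Statistical Power section): 60 villages per arm for each factor, m = 8 high-risk people per village (480 per arm), SD 15, ICC 0.05, difference 2.5 mmHg, alpha 0.05. Sidedness is not stated. Two-sided is assumed because the Analysis Plan reports 95% confidence intervals; one-sided results are also given. Beta = 0.90 is read as power 0.90.

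**Check of the method on salt** (m = 40, 2,400 per arm, follow-up levels)
- Design effect = 1 + 39 × 0.05 = 2.95
- SE = √(2 × 225 × 2.95 / 2400) = 0.744 mmHg
- 2.5 / 0.744 = 3.36, giving power of 92%. The stated salt figure is reproduced.

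**Package, follow-up levels**
- Design effect = 1 + 7 × 0.05 = 1.35
- SE = √(2 × 225 × 1.35 / 480) = 1.125 mmHg
- 2.5 / 1.125 = 2.22, giving power of 60.3% (59.6% using t with 118 df)

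**More favourable readings of the same inputs**

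| Reading | Two-sided | One-sided |
|---|---|---|
| Clustering as stated | 60% | 72% |
| Village-level adjustment for baseline | 60–64% | at most 75% |
| No clustering, SE = √(2 × 225 / 480) = 0.968 | 73% | 83% |
| Blocking removes all between-village variance, SE = √(2 × 225 × 0.95 / 480) = 0.944 | 75% | 84% |

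None reaches 90%.

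**Package, net pre-post difference, independent samples of 8 per village at each survey**

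Variance = 225 × (2/60) × [2 × 0.05 × (1 − r) + 2 × 0.95 / 8]. Here r is the correlation of a village's effect between the two surveys. The protocol gives no value, so the whole span is shown.
- r = 0: SE = 1.591, power 34.9% (34.4% by t)
- r = 1: SE = 1.335, power 46.5% (45.9% by t)
- One-sided: 47% to 59%

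**Difference detectable with 90% power** (3.24 × SE, two-sided)
- Follow-up levels: 3.24 × 1.125 = 3.65 mmHg. Doubled for half managed: about 7.3 mmHg.
- Net difference: 4.33 mmHg (r = 1) to 5.16 mmHg (r = 0). Doubled: about 8.7 to 10.3 mmHg.

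**What 90% power at 2.5 mmHg would take** (follow-up levels). Changing one input at a time, it needs an SD of about 10.3 mmHg, or about 33 high-risk people per village, or 757 × 1.35 / 8 ≈ 128 villages per arm.

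**Salt, net difference.** SE runs from 1.052 (r = 0, power 66%) to 0.597 (r = 1, power 99%). Power exceeds 90% once r is about 0.68 or more, from 7.5 × [0.1(1 − r) + 0.0475] = (2.5 / 3.24)².

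**The case against.** The arithmetic for the package could not be rescued, but several points on the other side deserve weight.

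- **Which comparison counts.** The Analysis Plan puts the follow-up comparison first and introduces the net difference as an addition. On that reading, 34% to 47% describes a supplementary analysis, and it rests on a correlation the protocol does not give. This stands: 60% is the headline figure. The Statistical Power section does, however, word its claim as a net difference.
- **The authors expect more than 2.5 mmHg.** The section cites drug effects of at least 10 mmHg. With half managed, that is 5 mmHg overall, where power is about 99% at follow-up and 88% to 96% for the net difference (5 / 1.591 = 3.14; 5 / 1.335 = 3.75). This stands too: the trial is not short of power at that larger effect. But the power statement is made at 2.5 mmHg, which the protocol treats as the smallest effect of policy interest.
- **Confidence intervals will be reported**, which limits misreading of a null result. True, but the planning figure would still mislead anyone judging the design.
- **Salt.** Its figure holds at follow-up, and for the net difference if r is about 0.68 or more. The protocol does not show it to be wrong.
- **Notation.** Writing "alpha=0.05, beta=0.90" where power is meant is an editorial slip; the later sentences make the intent clear.

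**Conclusion.** The concern holds. On the protocol's own inputs, the package comparison has about 60% power to detect 2.5 mmHg at follow-up, against a stated figure above 90%. A true effect at the policy threshold would be missed about 40% of the time. For the net pre-post difference, it would be missed more than half the time.

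The 60% assumes two-sided testing and nothing else from outside the protocol; one-sided testing gives 72%. The 34% to 47% range covers every between-survey village correlation from 0 to 1 and both the t and normal calculations. Where the error arose cannot be told from the document. One coincidence is that 960 people in each arm with no clustering would give 95%, but the protocol states 960 in total and an ICC of 0.05.

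The salt figure is right for follow-up levels and conditional for the net difference. It is a side note, as is the beta notation.

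**What to change.** In the Statistical Power section:

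- Replace the package figure with about 60% power for 2.5 mmHg on the comparison of follow-up levels, and 90% power for about 3.7 mmHg (about 7.3 mmHg in those managed).
- State which comparison is primary, follow-up levels or net difference, and base both power statements on it. If the net difference is kept, give the assumed correlation of village effects between surveys. For the package, report power within 34% to 47% and a 90% detectable difference of 4.3 to 5.2 mmHg.
- For salt, state 92% for follow-up levels, or the conditional figure for the net difference.
- Say openly that the package comparison is underpowered at the 2.5 mmHg threshold. If 90% power there is a requirement, the number of villages or of high-risk people per village has to change.
- Change beta = 0.90 to power = 0.90.

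Correcting the text costs only protocol wording and a less favourable stated power; no extra participants are needed for that. Restoring 90% power at 2.5 mmHg would be a different and much larger change: about 128 villages per arm in place of 60, or about 33 high-risk people per village in place of 8.
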